### Study design

This is a prospective, explorative, longitudinal multicentre observational study without any specific intervention. Different methodological components (mixed-method study; see sections A and B) are included. The aim of the study is to obtain an overview of the problems associated with the new disease COVID-19 to derive recommendations for future clinical practice.

The Institute for Social Medicine and Epidemiology at the University of Lübeck leads the study. Consecutive recruitment will occur in five different rehabilitation clinics in Germany (MEDIAN Klinik Heiligendamm, Reha-Zentrum Schömberg, Ostseeklinik Schönberg-Holm, MEDIAN Klinik Flachsheide Bad Salzuflen, MEDIAN Klinik Flechtingen). Each clinic designates a study representative who recruits suitable rehabilitants during their first days in rehabilitation. If possible, the study representatives personally contacted the study participants and provides them with the information material and the declaration of consent.

### A: quantitative measures

To measure the long-term burden of COVID-19 and the effects of rehabilitation, the study includes four measurement points: at the beginning (t_0_), at the end of rehabilitation (t_1_), six (t_2_) and twelve months after rehabilitation (t_3_). A questionnaire with standardised and validated instruments will be completed by all study participants at each measurement point.

In the rehabilitation clinics, the participants of both groups are recruited consecutively at the same time until the planned number of cases is reached.

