### Aims

The aim of our study is to describe the health status after COVID-19 in the context of medical rehabilitation and its medium- and long-term effects in different dimensions. For this purpose, the study examines the burden of disease and changes in health status under medical rehabilitation and after six and twelve months. Based on the experience of studies on pneumological rehabilitation, we expect positive effects on the general state of health and psychomental disorders at the end of rehabilitation. At follow-up, we expect that in addition to the outcomes already mentioned, rehabilitation success is represented in the dimensions of participation, quality of life, performance in various areas of life, ability to work, and subjective prognosis of employment.

Including rehabilitants from different clinics, it is possible to describe different therapeutic approaches, groups of patients and courses of disease. Statements are made about the extent to which existing rehabilitation approaches meet the needs of COVID-19 rehabilitants, the extent to which new rehabilitation therapy concepts have to be developed and how these are constituted. To date, it is unclear which requirements rehabilitants have with regard to aftercare, which recommendations rehabilitation clinics make and to what extent rehabilitants implement them.

The analyses also considered the severity of the disease course and compared the study results with a reference group with obstructive airway disease (COPD or bronchial asthma). Finally, the study will provide concrete recommendations for rehabilitation after COVID-19.

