### Intervention

As an observational study, there is no intervention in the strict sense. The rehabilitants receive medical rehabilitation directly following hospitalisation or with greater time after SARS-CoV-2 infection. The duration of rehabilitation is 21 days with the possibility of extension. Given that the study participants are recruited from different clinics, the rehabilitation programmes differ in terms of therapy concept and structure.

At the MEDIAN Klinik Heiligendamm, the therapeutic elements of rehabilitation include general strengthening, mobilisation and normalisation of respiratory functions. This is intended to improve respiratory distress, respiratory muscle strength, pulmonary resilience, psychomental impairments and/or stress-induced mental disorders of the disease. The main components of the therapy include respiratory gymnastics with respiratory muscle training as well as dissolving phlegm. If required, group discussions (1–2 h per week) are offered to exchange experiences of coronavirus disease, relaxation training and supportive psychological counselling to cope with trauma, fear or depression.

The Reha-Zenrtum Schömberg treats patients in the pneumology department after severe respiratory insufficiency caused by a respiratory disease (including bronchial asthma and COPD) and after pneumonia. With this experience, the rehabilitation centre also receives COVID-19 patients for rehabilitation. The therapy contents include physical and balneotherapy, physiotherapy and exercise therapy, occupational therapy and psychological support.

Ostseeklinik Schönberg-Holm offers medical rehabilitation for various respiratory diseases. These illnesses range from bronchial asthma and COPD to the novel disease COVID-19. This facility also pursues a multimodal and holistic treatment approach during pneumological rehabilitation.

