### Immediate expected results of the project

As this is an observational study, the baseline situation and the changes in the mentioned outcomes are described. These results are reported in relation to the comparison group, and statements on the extent to which there are similarities and differences are provided. The rehabilitation contents, needs and ability; aftercare recommendations and their implementation are also described descriptively for different degrees of disease severity.

Although the rehabilitants do not receive an intervention in the strict sense, they all undergo rehabilitation. Based on previous studies on pneumological rehabilitation as well as from the current experience of rehabilitation physicians, we expect positive changes in outcomes during rehabilitation. For example, we expect a significant reduction in the burden of disease and psychological impairments at the end of rehabilitation. The extent to which the effects on outcomes change over all four measurement points will be described in this study.

The results of the study will show whether rehabilitants have different needs in terms of rehabilitation, its contents and aftercare due to their individual course of illness, their previous illnesses or other personal prerequisites. With regard to aftercare, it is assumed that individual needs range from their own initiative and classic aftercare programmes to more intensive aftercare.

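### The protocol says it measures the effects of rehabilitation, but with no unrehabilitated COVID-19 group the design can only describe change, and the limitations do not say so

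*Protocol article*

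**What the plan says.** Effect wording appears in several places. The section on quantitative measures gives the purpose: "To measure the long-term burden of COVID-19 and the effects of rehabilitation, the study includes four measurement points". The Aims set out to "describe the health status after COVID-19 in the context of medical rehabilitation and its medium- and long-term effects in different dimensions" and expect that at follow-up "rehabilitation success is represented in the dimensions of participation, quality of life, performance in various areas of life, ability to work", among other dimensions. The Abstract says that the short- and long-term effects of such a programme are unknown and that the project investigates this question. The Discussion repeats that the effects have not yet been evaluated.

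The design is described differently. Study design calls it a "longitudinal multicentre observational study without any specific intervention". The section on immediate expected results states: "Although the rehabilitants do not receive an intervention in the strict sense, they all undergo rehabilitation". According to the Intervention section, the comparison group consists of COPD and asthma patients whose treatment is comparable to that of the COVID-19 patients. The same section says of entry: "The rehabilitants receive medical rehabilitation directly following hospitalisation or with greater time after SARS-CoV-2 infection". The quantitative analysis evaluates pre-post differences by repeated-measures analysis of variance and t-tests. Its planned subgroups are sex, age, education, risk factors and comorbidities.

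**The concern.** A claim about the effect of rehabilitation needs some information on how the same kind of patient would have fared without it, and no arm of this study supplies that. The Background itself says that persistent symptoms can vary in intensity over time. The Abstract says rehabilitation is offered after a severe course or when long-term impairment threatens. Some change without treatment is therefore plausible, and so is some regression to the mean, because people are measured first at a time when they are impaired enough to be admitted.

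The project is meant to end in concrete recommendations for rehabilitation after COVID-19, differentiated by severity where needed. If improvement is read as an effect, those recommendations would rest on a property that the design lacks. The Limitations section deals only with imbalance between the COVID-19 group and the comparison group; it mentions neither natural recovery nor regression to the mean.

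**Working it through.** **Step 1: the plan's own figures.** The sample size is based on precision, and it reproduces.

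- 95% half-width for a proportion at n = 100: 1.96 × √(0.10 × 0.90/100) = 5.9 percentage points, and 1.96 × √(0.40 × 0.60/100) = 9.6 points. Both are inside the stated limit of 10.
- Inflation: 100 × 1.2 = 120; 120/(1 − 0.20) = 150.
- Totals: 150 + 100 + 100 = 350 COVID-19 patients; 75 + 75 + 40 + 40 = 230 in the comparison group.

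These figures concern precision. They have no bearing on attribution.

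**Step 2: what the change contains.** Write the mean COVID-19 change as

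D = R + N + M,

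where R is the rehabilitation effect, N the natural course and M regression to the mean. The study observes D only. For the comparison group,

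D′ = R′ + N′ + M′,

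with a different, chronic disease and comparable rehabilitation. The contrast is

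D − D′ = (R − R′) + (N − N′) + (M − M′).

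Neither D nor D − D′ isolates R. The adjustment or propensity matching offered in the Limitations section balances measured characteristics between the groups. It does not supply an unrehabilitated COVID-19 course.

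**Step 3: illustration with R = 0.** Inputs: 350 × 0.8 = 280 COVID-19 completers (the plan's 20% dropout) and a two-sided 5% paired t-test. The drift N + M, in units of the SD of change, is an assumption and is not in the documents.

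- Smallest significant mean change: t(0.975; 279)/√280 = 1.97/16.73 = 0.118 SD of change.
- Probability of a significant result, from the noncentral t with noncentrality drift × √280:

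| Assumed drift (SD of change) | Noncentrality | P(significant, R = 0) |
|---|---|---|
| 0.1 | 1.67 | 39% |
| 0.2 | 3.35 | 92% |
| 0.3 | 5.02 | 99.9% |

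With the completers of the largest COVID-19 clinic alone (150 × 0.8 = 120), the same drifts give 19%, 58% and 90%. A larger sample makes a false attribution more likely. The table shows only that significance says nothing about cause; it does not estimate the bias.

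**Step 4: entry time.** The Intervention section describes entry both straight after hospital and later, and the eligibility criteria set no window. The subgroup list does not name time since infection. The Background places severe cases in follow-up rehabilitation and mild or moderate cases with long-lasting symptoms in rehabilitation as well. Entry time and severity are therefore probably entangled, and change shown by severity alone may partly reflect when patients were admitted.

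**The case against.** The best reply is that the operative text is already mostly descriptive. The quantitative analysis confirms no predefined hypotheses and mainly describes changes, the comparison group serves to classify the findings, and the recommendations come through an expert workshop and concern content, needs and aftercare. This stands in part and lowers the severity. It does not remove the point: exploratory status concerns hypothesis testing, whereas the effect and success wording makes a claim about cause, and nowhere does the article caution against that reading.

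Several stronger readings are tempting, and the documents do not support them.

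- *Natural recovery will be reported as success.* That is a forecast, and the descriptive passages point the other way.
- *The expectation of improvement contradicts the absence of hypotheses.* The sentence "we expect a significant reduction in the burden of disease and psychological impairments at the end of rehabilitation" states an expectation and its timing. It is neither a confirmatory hypothesis nor an attribution.
- *The Background shows fast natural resolution.* The figure of one in ten with persistent symptoms after three weeks concerns symptom-app users, not rehabilitation patients. The same section reports 143 hospitalised patients 60 days after first symptoms, of whom only 13% were symptom free and 55% had three or more symptoms.
- *Time since infection varies widely, or is the strongest driver of recovery.* No range is given, and nothing in the article ranks the drivers.
- *The infection date is not recorded.* Table 1 is a core set of instruments in a condensed article, clinics keep separate documentation, and the covariates under Limitations are given as examples. Absence from these lists does not show that the date is missing.

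**Conclusion.** The point holds as a mismatch between stated purpose and design: the article says that it measures effects of rehabilitation, while the design supports only a description of change in rehabilitated patients. This follows from the article's own statements on exposure, comparison group and analysis, and needs no assumption about how fast patients recover.

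The size of the bias cannot be derived from the documents. The probabilities of 39%, 92% and 99.9% rest on assumed drifts of 0.1, 0.2 and 0.3 SD of change, no rehabilitation effect and 280 completers. The point about entry time is narrower: the article describes different entry times and does not name them in its subgroup list. That entry time is confounded with severity is probable, not shown. The whole is a should-fix matter, because the descriptive wording already covers much of the ground and the remedy is small.

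**What to change.** 1. In the Aims and under the quantitative measures, replace the effect and success wording with change during and after rehabilitation, in line with the quantitative analysis section. Report that change with 95% confidence intervals.
2. In Limitations, state that the change cannot be attributed to rehabilitation, because natural recovery and regression to the mean cannot be separated from it, and that the comparison group is a descriptive reference only.
3. Add time from infection or symptom onset to admission, taken from clinic records, as a stratum or covariate for COVID-19 change, and show it alongside severity. Label this a descriptive sensitivity analysis. Early and late entrants probably differ in severity, and possibly in clinic and programme, so a larger change in early entrants would not isolate natural recovery.

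The cost is edited wording, one date item if it is not already held, and slightly more analysis. The downside is a weaker headline claim.

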#### Outcomes

Based on the International Classification of Functioning, Disability and Health (ICF), the IMET [17] measures the *restrictions for social and work-related participation* of persons with a chronic disease [18, 19]. The IMET is a valid instrument and assesses the limitations of participation in nine relevant dimensions of daily life. On a scale from 0 to 10, the respondent ranks how high their limitations are in each dimension. A high score is associated with limited participation. Both, individual items and the cumulative score can be evaluated.

The VR-12 measures *health-related quality of life (HRQoL)* at the beginning of rehabilitation and at catamnesis. The VR-12 is based on the SF-36 and the Veterans Health Study. It covers eight health domains, and a total score is provided [20]. We use the translated and culturally adapted German version, which was validated in a German sample of inpatient rehabilitation patients [21].

Core symptoms of *depression, anxiety and stress* are assessed with the DASS. The instrument is mainly used in patients with pain, but it is also used for patients without pain-specific symptoms. The short version in Germany comprises 21 items and 7 items for the respective scales of depression, anxiety and stress. The individual scales of the DASS have sufficient to good reliability and have also been classified as valid [22].

The presence of a *generalised anxiety* disorder as well as its symptom severity is measured using the GAD-7 [23]. For this purpose, 7 items are used according to the most important diagnostic criteria of generalised anxiety disorder as defined in the Diagnostic and Statistical Manual of Mental Disorders (DSM-IV). The response options from “not at all” to “nearly every day” indicate how often the problem occurred in the last two weeks. The scale has good reliability and validity.

*Depressiveness* is measured with the PHQ-9 [24], which is the depression module of the Patient Health Questionnaire (PHQ-D) and contains nine questions. Each item captures one of the nine DSM-IV criteria of “major depression”. According to a large-scale meta-analysis, the PHQ-9 has very good specificity and sensitivity [25].

The COPD Assessment Test (CAT) [26] assesses the *effects of chronic obstructive pulmonary disease*. The CAT is a reliable instrument designed to measure the impact of COPD on health status and daily life [27]. A semantic six-point differential scale is used for the eight items. Cough, phlegm, tightness, breathlessness going up hills/stairs, activity limitation at home, confidence leaving home, sleep and energy are measured with one item each.

The Work Ability Score (WAS) of the Work Ability Index (WAI) measures the *work ability*. In numerous studies, this score provided acceptable values in terms of validity and reliability [28]. The higher the score on the scale from 0 to 10, the higher the ability to work.

The German version of the SPE scale is used to predict the *subjective prognosis of employment*. To divide the study participants into two risk groups, the respondents assess their occupational risk with three items from which an overall score is formed. The validity and reliability of the SPE scale was positively evaluated in a large sample [29].

Using individual items, *occupational changes* are measured, including job retention interventions and types of job loss [30].

*Fatigue* is measured with the EORTC-FA12, which has been validated in large international and multicentre studies [31]. With the help of twelve four-stage items (“not at all” to “very much”), physical, emotional and cognitive impairments caused by fatigue are assessed. In a German study validating the questionnaire with breast cancer patients [32], a high consistency of the overall scale was observed; the subscale also shows good to high internal consistency [32].

Single items without standardisation capture *COVID-19-associated life events*. Questions are asked about the death of a relative due to COVID-19, COVID-19-associated physical and/or social deprivation, loss of autonomy and loss of economic livelihood. Participants are also asked if they infected someone else, how they feel about it and if they feel that their general practitioner takes their symptoms seriously.

*Performance in different areas of life* is assessed with three scales from 0 to 10 for the areas of work, everyday life and leisure. The individual scales are valid instruments for determining performance limitations. A low sum score indicates a high level of performance limitations [30, 33].

To assess the extent of *physical activity*, questions are asked in conjunction with Menski’s Federal Health Surveys [34].

The moderating variables include comorbidity [35], risk factors and sociodemographic variables [36].

The rehabilitants receive the questionnaires at four measurement points. Some of the outcomes that are not likely to change during rehabilitation are only measured at the beginning of rehabilitation and at catamnesis. These are parameters that probably change only insignificantly during rehabilitation (e.g., comorbidities) or outcomes addressing everyday life and the domestic environment. Table 1 presents the set of core instruments used in the study.

**Table 1 Tab1:** Core set of instruments used in the quantitative part of the study

Dimensions	Instruments	t_0_	t_1_	t_2_	t_3_
Restriction of Participation	IMET [17]	●		●	●
Quality of Life	VR12 [20]	●		●	●
Depression, Anxiety and Stress Scale	DASS [22]	●	●	●	●
Stress-Related Psychomental Limitations and Disorders	GAD-7 [23]; PHQ-9 [24]	●	●	●	●
Corona-associated Life Events	Single Items	●	●	●	●
Effects of Chronic Obstructive Pulmonary Disease	CAT [26]	●	●	●	●
Fatigue	EORTC-FA 12 [32]	●	●	●	●
General State of Health	Single Items	●	●	●	●
Performance in Various Areas of Life	QGmR [30]	●		●	●
Occupational Changes	Single Items from QGmR [30]			●	●
Occupational Situation	Single Items	●		●	●
Ability to Work	Work Ability Score, WAS [28]	●		●	●
Subjective Prognosis of Employment	SPE-Scale [29]	●		●	●
Moderating Variables					
Comorbidity	Single Items [35]	●		●	●
Risk Factors	Single Items	●	●	●	●
Sociodemographic Data	Single Items [36]	●		●	●

*t*_0_baseline/right before rehabilitation; *t*_1_ 3-week follow-up/right after rehabilitation; *t*_2_ 6 months after rehabilitation, *t*_3_ 12 months after rehabilitation

### B: qualitative measures

Telephone interviews and an expert workshop occur during the study. The guidelines for the telephone interview were pre-tested with COVID-19 rehabilitants. Rehabilitants provided feedback on the comprehensibility of the questions and the length of the interview.

Regarding telephone interviews, nine rehabilitants after COVID-19 were interviewed at three points in time: after medical rehabilitation, six and twelve months after rehabilitation. In the comparison group, eight interviews were held six months after rehabilitation. The interview participants varied in terms of sex, age and educational background.

 In the semi-structured interviews, the participants were asked about the course of their disease, the contents and goals of their rehabilitation, their satisfaction, their current disease burden, their social and occupational participation and their rehabilitation aftercare.

The expert workshop involves clinical staff, funding agencies and scientists. The topics of the workshop include the rehabilitation procedure, general conditions of rehabilitation after COVID-19, and existing pneumological therapy concepts in rehabilitation. Finally, recommendations for rehabilitation after COVID-19 are formulated.

Both the interviews and the expert workshop follow guidelines. The guidelines and the results of the qualitative research are discussed by the project team and at the brain trust “Arbeitsgruppe qualitative Methoden” (AQUAM). The interviews last approximately 30 min, while the expert workshop is correspondingly longer. With the agreement of all participants, the interviews and the workshop are recorded and transcribed word by word. The evaluation of data is based on qualitative content analysis.

### Data management

#### Patient documentation

Study participants are uniquely organised and documented in all clinics using an automated documentation template. All study representatives are briefed on the template before recruitment.

The included study participants receive an identification number (ID) to pseudonymise their personal data. The first number is used to classify whether the participant receives rehabilitation after COVID-19 or belongs to the comparison group. The second number of the ID refers to the rehabilitation clinic where the participant is recruited. The subsequent numbering corresponds to the number of recruited participants. Personal data are only documented in a separate Excel file; appropriate linkage occurs using the ID. The data will not be sent to the ISE until the personal contents are deleted. This collection includes only standardised documentation in the clinics. The data from the questionnaire are collected and kept separately from the ISE.

